### Randomisation

Randomisation is executed at the research center at practice-level, without any stratification. It is not possible to blind participants and GPs for the treatment allocation. Practices are randomised a second time, i.e. intervention practices in the ADDITION study could be control practices in the current study and vice versa.

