### Control group

Patients in the control practices will receive treatment-as-before. Also, the GPs will not be asked to engage in a SDM process, nor be trained to do this and they will not be offered the decision support tool. The GP will treat the patients as they were used to since the ending of the ADDITION study (2009), either following the national guidelines or the ADDITION intensive treatment algorithm, each with their respective targets [1].

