### Measurements, data collection

Data about the patient’s socio-demographic background, the level of education, smoking status and whether the patient lives alone or together will be collected by patients’ self-report at baseline. HbA1c, blood pressure, body weight, total cholesterol and LDL-cholesterol, and smoking habits as well as patient characteristics (age, gender, duration of diabetes and comorbidities) will be reported every year by the GPs on a specific Case Report Form in both groups.

Blood pressure is measured by two measurements after at least 10 minutes rest, while participants are seated with the cuff on the predominant arm at the level of the heart, using an automatic sphygmomanometer. Height and body weight are measured in light indoor clothing and without shoes using a fixed rigid stadiometer and a scale respectively. Laboratory results (HbA1c, LDL-cholesterol) were obtained with case report from the GPs electronic records.

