### Sample size

As stated in the Introduction, only 10-15% of T2DM patients achieve all three treatment targets for both HbA1c, lipids and blood pressure. We estimate the percentage of patients that already has reached three targets at the start of the study will be approximately 10%. We hypothesise that in the OPTIMAL study, after two years of follow-up, the intervention group will show an increase of this percentage until 30% (about 10% increase per year), whereas in the treatment-as-before-group this percentage will stay at 10%. Assuming a two-sided significance level of 5%, with alpha 0.05 and power of 80% and with a drop-out of 10%, 65 patients will be needed in each treatment group (Department of Statistics Sample Size Calculator, University of British Columbia). Because the OPTIMAL study is a cluster randomised study the sample size will require an correction for the cluster effect. The used correction factor is equal to [1 + (m - 1) r], where ‘m’ is the total amount of eligible patient per practice (approximately 6), and ‘r’ the within-cluster correlation coefficient. For ‘r’ we use a within-cluster correlation coefficient of 0.025, based on the cluster correlation found in the ADDITION-Europe study. When taken the cluster effect (1.125) in to account, 73 patients per group are needed.

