### Statistical analyses

Intention-to-treat analyses (ITT) will be performed to examine between-group differences. Generalized linear models will be used to correct for clustering at practice level. The proportions of achieved treatment goals of HbA1c, blood pressure, LDL-cholesterol within each study group will be estimated by calculating relative risk. The same applies to the difference between groups in the proportion of patients which achieved all the five above mentioned treatment goals. A p-value of <0.05 is considered statistically significant. To identify patients who show better results after the SDM process, the analysis for the primary outcome will be repeated with taken into account interaction of SDM with age, gender, education level, duration of diabetes and comorbidities. Within and between group differences in treatment satisfaction, perceived quality of life, health status, well-being, and coping style between baseline and 24 months follow-up will be analysed by using paired t-tests and mixed models respectively. We will add random effects for patient and practice.

The SDM-Q9 will be analysed in the intervention group by using paired t-tests. Mixed models will be used to study the between groups differences after 24 months. We will add random effects for patient and practice.

To evaluate the SDM proces, the tapes will be evaluated by two independent observers by making use of the SDM-Q9.

The Medical Research Ethics Committee of the University Medical Centre Utrecht has approved the study protocol (Protocol number: 11-153).

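### Practices are allocated without stratification and the stated primary model corrects only for clustering, so the former ADDITION arm and baseline risk-factor values, both plausibly prognostic, go unused

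*Protocol article*

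**What the plan says.** The article's Randomisation section states: "Randomisation is executed at the research center at practice-level, without any stratification". It adds that practices are randomised a second time, so a practice from either ADDITION arm can fall in either OPTIMAL arm.

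The Control group section says that control GPs carry on as they have since ADDITION ended, "either following the national guidelines or the ADDITION intensive treatment algorithm", each with its own targets. The abstract likewise has controls continuing the treatment they were allocated to in ADDITION.

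For the between-group comparison, the Statistical analyses section says: "Generalized linear models will be used to correct for clustering at practice level". Age, gender, education, diabetes duration and comorbidities appear only as interactions with the intervention in a repeat of the primary analysis. Former ADDITION arm and baseline clinical values are not named for the primary comparison.

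Those values are held. Under Measurements, data collection, the risk-factor values and patient characteristics "will be reported every year by the GPs on a specific Case Report Form in both groups".

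**The concern.** The former ADDITION arm was fixed for each practice before re-randomisation. In the control group it bears on both the care given and the targets that patients are treated to. If one OPTIMAL arm receives more formerly intensive practices by chance, part of the observed difference may reflect that split and not shared decision making. With only 40 units to allocate, such a split is a realistic possibility.

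Baseline HbA1c, blood pressure and cholesterol are earlier measurements of the components of the primary endpoint, so they plausibly predict the 24-month result. A model without them gives up precision that could be had at little cost, in a trial sized with little margin. Naming the adjustment in advance also removes the temptation to choose one after an imbalance has been seen.

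**Working it through.** **Inputs from the article.** 10% of patients at all three goals at baseline and in controls at 24 months; 30% in the intervention group; two-sided 5% level; 80% power; 10% dropout; m = 6 patients per practice; within-cluster correlation 0.025 (all Sample size). 40 practices and 150 patients (abstract).

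**Assumed, because the article does not give them.** 20 practices from each former arm and 20 allocated to each OPTIMAL arm; goal rates by former arm; the correlation r between baseline measure and 24-month outcome.

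**1. The plan's own figure.** Unpooled formula: (1.96 + 0.84)² × (0.10×0.90 + 0.30×0.70) / 0.20² = 58.9. Dividing by 0.9 gives 65.4, so 65. Design effect: 1 + 5 × 0.025 = 1.125; 65 × 1.125 = 73.1, so 73. The stated 65 and 73 per group reproduce, and this point does not make them wrong.

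**2. Chance of imbalance on former arm.** Let X be the number of formerly intensive practices in the intervention arm, hypergeometric (40, 20, 20).
- P(X = 10) = 0.2476; P(X = 9) = P(X = 11) = 0.2047.
- P(12 versus 8 or worse) = 1 − 0.2476 − 2 × 0.2047 = 0.343.
- P(X = 8) = P(X = 12) = 0.1151, so P(13 versus 7 or worse) = 0.343 − 0.230 = 0.113.
- P(14 versus 6 or worse) = 0.026.

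If practices were allocated by independent coin flips, the chances of a gap of at least 20, 30 or 40 percentage points in the formerly intensive share are 27%, 8% and 1.7%.

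**3. What an imbalance would do.** Shift in the estimated difference = gap in formerly intensive share × difference in goal rate between former arms (assumed).

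| Split | Gap | Rates differ by 5 points | by 10 | by 20 |
|---|---|---|---|---|
| 12 v 8 | 20 points | 1 | 2 | 4 |
| 13 v 7 | 30 points | 1.5 | 3 | 6 |
| 14 v 6 | 40 points | 2 | 4 | 8 |

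The planned effect is 20 points.

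**4. Chance imbalance in baseline goal status.** With 75 per arm and 10% at goal, SE = √(2 × 0.10 × 0.90 / 75 × 1.125) = 5.2 points, a 95% range of about ±10 points.

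**5. Power gained by baseline adjustment.** Effective n per group = 73 × 0.9 / 1.125 = 58.4. Pooled-variance test: z = (0.20 × √58.4 − 1.96 × √(2 × 0.20 × 0.80)) / √0.30 = 0.766, power 77.8%. This is just under 80% because the plan's 65 rests on the unpooled formula. Adjustment multiplies the variance by 1 − r², so n becomes 58.4 / (1 − r²):

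| r (assumed) | Variance factor | Power |
|---|---|---|
| 0 | 1.00 | 77.8% |
| 0.2 | 0.96 | 79.5% |
| 0.3 | 0.91 | 81.6% |
| 0.4 | 0.84 | 84.6% |
| 0.5 | 0.75 | 88.5% |

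**6. Events available to support covariates.** Completers per group: 73 × 0.9 = 65.7. Expected events: 65.7 × 0.10 + 65.7 × 0.30 = 6.6 + 19.7, about 26.

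**The case against.** The best case for the plan is that simple randomisation is valid, that chance imbalance is not systematic bias, and that the article condenses a plan whose covariate list may be set out elsewhere. The first two stand in full. The third weakens the point about the missing baseline term, but not the absence of stratification, which is stated outright; the article also describes the primary model and gives clustering as its only correction.

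Several stronger readings are tempting but unsupported:

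- **That these factors are strongly prognostic.** The article gives no goal rate by former arm and no baseline-to-outcome correlation. Former arm is not identical to current regimen: ADDITION ended in 2009, the article allows for patients changing treatment since, only half the participants were in ADDITION, and intervention patients choose their option. The statement that the two treatments can theoretically be equally effective does not settle it either way, because it rests on cardiovascular events and death, not goal attainment.
- **That a material imbalance is likely.** On the assumed numbers, 66% of allocations are 11 versus 9 or better.
- **That mixing two regimens breaks the sizing.** Former-arm rates of 5% and 15% (assumed) alone imply a correlation of 0.05² / (0.10 × 0.90) = 0.028, above the 0.025 used. But the article does not say whether 0.025 was estimated within arms. At 150/40 = 3.75 patients per practice, even the sum gives 1 + 2.75 × 0.053 = 1.146, against the planned 1.125.
- **That the larger power gains can be counted on.** For a yes/no baseline status at 10% and an outcome at 30%, r cannot exceed √(0.10 × 0.70 / (0.90 × 0.30)) = 0.51. Reaching 0.5 requires about 99% of baseline achievers to stay at goal; 0.4 requires about 85%. A 0–3 count or the measured values escape that cap, but no r is given for them.
- **That baseline is also ignored for the questionnaires.** The Statistical analyses section already analyses differences between baseline and 24 months.

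**Conclusion.** The point holds as a matter of efficiency and protection against chance, not validity. The stated design and primary model leave unused a practice-level factor known before randomisation and baseline values that are already collected.

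On an assumed 20:20 composition, the chance of a 12 versus 8 split or worse is 34%, and of 13 versus 7 or worse 11%. If former-arm goal rates differ by 5 to 10 points, splits from 12 versus 8 to 14 versus 6 would move the estimate by 1 to 4 points against a planned 20. Power would rise from 77.8% to between 79.5% and 88.5% for r from 0.2 to 0.5. At the lower end the gain is small; it becomes substantial only from about r = 0.4.

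A reader might infer that the trial's result would be biased or its sample size wrong. Neither follows: the allocation is unbiased and the stated sample size reproduces.

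**What to change.** The Study design section reports that intervention GPs were trained, so allocation appears to be done and the practical remedy is in the analysis. Before unblinded data are examined:

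1. Add to the primary model the former ADDITION arm of the practice and one baseline measure.
2. Make the baseline measure independent of targets chosen after randomisation. Intervention patients choose their option, and with it their targets, at the first visit. Baseline status scored against those targets could itself be affected by allocation. Use either the number of goals met (0–3) against one fixed target set applied to everyone, or baseline risk-factor values. The count uses one parameter; separate values for each risk factor would use more, so a single summary suits the expected number of events better.
3. Report the covariate-standardised risk difference and relative risk, with the unadjusted result as supportive.
4. Leave patient source (former ADDITION participant or not) to a sensitivity analysis.
5. State a fallback for non-convergence, for example a logistic model with standardisation that still accounts for practice, then removal of covariates in a fixed order.

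**Cost.** Analysis wording only; no new data. There is a real downside: with about 26 expected events, a clustered relative-risk model with many terms risks non-convergence and sparse-data bias. That is why covariates should be held to one or two.

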### Intervention

The decision support tool.The OPTIMAL decision support tool is a simple paper-based tool, aimed to be easy to use for both the GP and the patients. It should be used to discuss the treatment options and the prioritising of treatment targets during the first visit and the 12- and 24-months follow-up visits. The tool consists of three steps: 1) considering the pros and cons of two almost equally effective evidence based multifactorial treatments, namely the intensified ADDITION protocol and the protocol derived from the 2006 Dutch guidelines for GPs [1] (for details see Figure 2, step 1b), and the shared decision on which option will be chosen; 2) prioritising of treatment targets according to the chosen option, and 3) treatment selection (medication or lifestyle) to achieve the treatment targets. For detailed information about the two treatment options and the different targets see Figure 2.

**Figure 2 Fig2:**
[figure not shown]
**Decision support tool.**Visits during the OPTIMAL study.During the first visit, and guided by the decision tool, the GP and the patient discuss the two evidence based T2DM treatments. The GP will explain the pros and cons of each option, and the treatment targets that should be achieved, depending on the option that is chosen. The GP should explain that both treatments are equally suitable for treating T2DM. Next, the patient’s preferences and lifestyle habits are discussed against the background of the patient’s most recent values of HbA1c, lipids, blood pressure, body weight and smoking habits. Then the GP and the patient will together decide on the preferred treatment option and the accompanying treatment targets. For a patient who underwent the intensified treatment in the ADDITION study and did not change it after the end of ADDITION, this visit provides him/her the opportunity to choose a less intensive treatment. Also the other way around is possible. The patient will prioritise the five treatment targets (HbA1c, cholesterol, blood pressure, body weight, smoking habits) for the first 12 months. The target with the highest priority will get the most attention and require the most effort of both the patient and GP. There will be no pre-defined way in how the patients should reach their targets; the patient and the GP need to determine this way together in a final step in the decision process. The patient and GP decide whether medication changes and/or lifestyle changes should be made in order to reach the prioritised targets. During the second and third OPTIMAL visit (12 and 24 months later) the patient and GP evaluate the decisions they made during the first visit using the decision support tool. The priority of the treatment targets can be changed during these visits, but not the choice between the two treatment options (ADDITION protocol or the less intensive protocol). During the third and final visit the patient and the GP will decide whether or not to keep to the chosen treatment option. Between the first and third visit, three monthly T2DM visits will take place either with the GP or the practice nurse.

### Training

The GPs from the practices randomised to the SDM-treatment arm are trained in the SDM approach during a two hours training session. During this session the study protocol is discussed as well as the SDM principle (see further) and the OPTIMAL decision support tool. By use of role-plays the SDM process will be practiced by the GPs.

### Control group

Patients in the control practices will receive treatment-as-before. Also, the GPs will not be asked to engage in a SDM process, nor be trained to do this and they will not be offered the decision support tool. The GP will treat the patients as they were used to since the ending of the ADDITION study (2009), either following the national guidelines or the ADDITION intensive treatment algorithm, each with their respective targets [1].

### Outcome measures

Primary outcome will be the proportion of patients that achieve all the three treatment goals for HbA1c, blood pressure, and total cholesterol .In addition to identify determinants of better performing patients for the primary outcome will be performed taken into account the interaction of SDM with age, gender, education level, duration of diabetes and comorbidities.

Secondary outcomes:The proportion of patients that achieve the all five treatment goals for HbA1c, blood pressure, total and LDL- cholesterol, body weight, and smoking.The following patient reported outcomes: diabetes treatment satisfaction, perceived quality of life, health status, well-being, and coping style.A process evaluation of the shared decision making ability of the general practitioners during the complete study. Outcome on GP level: the level of SDM-knowledge/attitude.

### Measurements, data collection

Data about the patient’s socio-demographic background, the level of education, smoking status and whether the patient lives alone or together will be collected by patients’ self-report at baseline. HbA1c, blood pressure, body weight, total cholesterol and LDL-cholesterol, and smoking habits as well as patient characteristics (age, gender, duration of diabetes and comorbidities) will be reported every year by the GPs on a specific Case Report Form in both groups.

Blood pressure is measured by two measurements after at least 10 minutes rest, while participants are seated with the cuff on the predominant arm at the level of the heart, using an automatic sphygmomanometer. Height and body weight are measured in light indoor clothing and without shoes using a fixed rigid stadiometer and a scale respectively. Laboratory results (HbA1c, LDL-cholesterol) were obtained with case report from the GPs electronic records.

Participants in both groups will be asked to complete and return the following questionnaires baseline and after 24 months at home.the Diabetes Treatment Satisfaction Questionnaire (DTSQ) [30] which includes 8 items; scores range from 0 (very dissatisfied) to 6 (very satisfied), totally from 0 to 48. The DTSQ is reliable, valid and sensitive to change in diabetes patients [30];the Audit of Diabetes Dependent Quality of Life (ADD QoL-19), which measures the perceived impact of diabetes on the quality of life; it includes 19 items, ranging from -3 to 3 on different questions, with 0 as the neutral score. Scores below 0 reflect a negative influence of the item on quality of life, and all above 0 reflect positive influences. The impact scores are weighted (impact rating x importance rating), so the actual scores per item can range from -9 to 9. The ADDQoL-19 has good psychometric properties and provides clinicians and researchers with a useful tool for comprehensively assessing quality of life in adults with T2DM [31];the Well-Being Questionnaire (W-BQ12) that consists of 12-items in three 4-item subscales: negative well-being (item 1-4, higher score reflects a greater sense of negative well-being), energy (items 6 and 7 are reversed, and then together with 5 and 8 form the total amount of energy) and positive well-being (items 9-12, the higher the score the greater the sense of positive well-being). The total score ranges from 0 to 36 and is called the general well-being score. Higher scores indicate a higher overall sense of well-being [32];the European Quality of Life (EQ-5D) questionnaire, that covers 5 dimensions (mobility, self-care, usual activities, pain/discomfort and anxiety/depression) and a Visual Analogue Scale (VAS) where respondents can rate their health. Item scores range from 1-3, and a 5-digit health profile is formed, placing the 5 numbers behind each other. It is a well-validated, reliable and responsive instrument for health measurement in patients with a wide range of medical conditions. Values found in the UK have been validated for the Netherlands [33-35];the Short Form-36, a validated 36-item instrument for the self-evaluation of health status with eight subscales: Physical Functioning (10 items), Role Physical (4 items), Bodily Pain (2 items), General Health (5 items), Vitality (4 items), Social Functioning (2 items), Role-Emotional (3 items) and Mental Health (5 items). These scales can be summarised in Physical Health and Mental Health. The 36 items differ in the scoring ranges. The Dutch version has proved to be a practical, reliable and valid instrument [36,37];the Diabetes Coping Measurement Questionnaire (DCMQ), consisting of 21 items in 4 subscales: spirit coping, avoidance coping, passive resignation coping and diabetes integration coping. Overall scores range from 7 to 35. The items are measures on a 5-point Likert scale, ranging from 1 (“disagree”) to 5 (“agree strongly”) or the other way around from 1 (‘I strongly agree’) to 5 (I ‘disagree’). Higher scores on tackling spirit and diabetes integration indicate more adaptive coping. Higher scores on passive resignation and avoidance indicate poor coping [38].

A process evaluation of the shared decision making ability of the general practitioners will be measured in the intervention group at baseline and after 12 months, and in both treatment groups at 24 months. Both the patients and GPs will be asked to complete The Shared Decision Making Questionnaire, both the patient (SDM-Q9-patient) and GP (SDM-Q9-doc) version will be used to evaluate this process.

The Shared Decision Making Questionnaire (both SDM-Q9 versions) [39-41] includes 9 items with ratings from 0 (completely disagree) to 6 (completely agree); the total score ranges from 0 to 54. It is a continuous scale, and the questionnaire developers did not describe any thresholds for ‘bad’ or ‘good’ SDM. Over the last years the SDM-Q9 has become a frequently used instrument in clinical practice. It has been translated into several languages. Internal consistency has been assessed for the Spanish and Dutch version (Rodenburg-Vandenbussche S, Pieterse AH, Kroonenberg PM, Stiggelbout AM,et al.: Further validation of the SDM-Q-9 and SDM-Q-Doc: psychometric properties in Dutch patients from primary and secondary care. Submitted). Item discrimination parameters were above 0.4 for all but one item. An analysis of internal consistency yielded a Cronbach’s α of 0.88 [39]. The Dutch version is currently being validated [41]. A modified version of the Control Preferences Scale (CPS) is used to determine the experienced role of decision making of the GP and patient. The CPS measures at a 5-point Likert scale, and has shown good reliability and validity [41,42]. The original Control Preference Scale by Degner [41], was developed to measure preference for involvement and is one of the most commonly used instruments to assess preferred decisional role [41,42].

Subsequently, the GPs of both groups (the intervention group trained, the control group not) will audio- or videotape one of their yearly consultations with a T2DM patient. They can choose the consultation to be taped themselves. These tapes will be evaluated by two independent observers, making use of the SDM-Q9, to assess the extent to which the GP is likely to involve his/her patients in the diabetes treatment.

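### Each unblinded GP picks the one consultation to be taped, so the only observer-rated SDM measure may not represent usual practice and selection may differ by arm

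*Protocol article*

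**What the plan says.** The protocol article describes the taping under Measurements, data collection. It applies to "the GPs of both groups (the intervention group trained, the control group not" (the control arm being untrained), and each GP "will audio- or videotape one of their yearly consultations with a T2DM patient". The selection rule follows directly: "They can choose the consultation to be taped themselves". On scoring it says: "These tapes will be evaluated by two independent observers, making use of the SDM-Q9". The stated purpose is "to assess the extent to which the GP is likely to involve his/her patients in the diabetes treatment". The Statistical analyses section repeats that "the tapes will be evaluated by two independent observers by making use of the SDM-Q9", as part of evaluating the SDM process, and names no test comparing tape scores between arms.

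The Randomisation section states: "It is not possible to blind participants and GPs for the treatment allocation". The Training section says that intervention GPs are taught the SDM principle and practise it in role-play; the Control group section says that control GPs are not trained.

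The other SDM measures are questionnaires completed by those taking part: SDM-Q9 in patient and doctor versions, and a modified Control Preferences Scale for the experienced decision role. SDM-Q9 is compared between arms at 24 months with mixed models.

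**The concern.** The tapes are meant to show how far a GP tends to involve patients, which is a statement about usual behaviour. A consultation picked by the GP estimates that only if the choice is unrelated to how well SDM goes in that visit, and nothing in the rule ensures this.

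There is a second layer. GPs choose knowing their allocation, and only one arm has been taught what SDM looks like. Trained GPs may be better placed to foresee which patient and visit will display it. If so, selection acts more strongly in one arm, and the difference between arms mixes a change in practice with a difference in choosing.

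At stake is the one SDM measure that unblinded patients or GPs do not report themselves. It could have served as a check on the questionnaires, and the selection rule weakens it for that purpose.

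**Working it through.** The plan gives no figure for the tape scores, so there is none to reproduce. The check has two parts.

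**1. Reading the sections together**

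- Who chooses: the GP, in both arms (Measurements, data collection). No random, consecutive or central selection is stated.
- How many: one consultation. The wording could mean one in all or one per year; a single tape is the natural reading.
- Knowledge of allocation: GPs are not blinded (Randomisation).
- Ability to recognise SDM: trained in one arm only (Training; Control group).
- Other SDM measures: all self-reported.

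The rule thus permits selection, and the arms differ in a feature that could affect it. The document does not show that such selection will occur.

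**2. Illustration of size**

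The following inputs are assumptions. A GP has k comparable visits to choose from. Their observer scores vary around the GP's own mean with a within-GP SD of 1 (standard normal). The GP tapes the visit that he or she ranks highest, and that ranking correlates ρ with the observer score. The document gives neither k nor ρ. Pools of 4 to 6 are taken because the Sample size section puts eligible patients at about 6 per practice.

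Expected inflation of the taped score over the GP's average visit = ρ × E(maximum of k standard normals). By simulation the expected maximum is 1.03 for k = 4 and 1.27 for k = 6.

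| ρ | k = 4 | k = 6 |
|---|---|---|
| 0 | 0 | 0 |
| 0.3 | 0.31 | 0.38 |
| 0.5 | 0.52 | 0.63 |
| 0.8 | 0.82 | 1.01 |
| 1 | 1.03 | 1.27 |

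Bias in the difference between arms = inflation (intervention) − inflation (control), in within-GP SD:

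- Same k and ρ in both arms: 0, for any k and ρ. Each arm's level is still overstated when ρ > 0.
- k = 4, ρ = 0.8 in the intervention arm and 0.3 in the control arm: 0.82 − 0.31 = 0.51, about 0.5 SD.
- The same values with the arms exchanged: 0.31 − 0.82 = −0.51, so the sign is not fixed either.
- Extreme case, k = 4, perfect ranking in the intervention arm and none in the control arm: 1.03 − 0 = 1.03.

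The document gives no within-GP SD for observer-rated SDM-Q9, so these values cannot be turned into points on its 0 to 54 scale.

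**The case against.** The same rule applies to both arms, and control GPs also know that their tape will be rated, so inflation may be similar and cancel. The choice is naturally read as made before recording, not as picking the best of several finished tapes. Perfect ranking is then implausible, and the upper figures are bounds rather than expectations. Both arguments stand. They are why the result is a range starting at zero.

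The article describes the process evaluation as one of SDM ability. What a GP can do in a chosen visit bears partly on ability, and recognising an occasion for SDM may itself be partly an effect of training. This also stands in part, but the stated purpose of the tapes is how far the GP is likely to involve patients, and that needs a typical visit.

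The tapes are a supplement. The SDM comparison between arms that the analysis section specifies is the self-reported SDM-Q9 at 24 months; a comparison of tape scores is only implied by taping both arms. That limits the weight of the point. It does not remove it, because the tapes are the only observer-rated evidence.

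An article condenses a fuller protocol, but this does not help here: the self-selection rule is stated, not left out. It does apply to observer masking, on which the article is silent and which cannot be called an error.

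Two stronger readings are tempting. A reader might infer that the tapes will be showcase visits; the article allows free choice and does not say that GPs choose their best. A reader might also infer that the tapes are the measure for the GP-level outcome ("Outcome on GP level: the level of SDM-knowledge/attitude") and for the third research question. The article never makes that link; it ties the tapes to involvement of patients and the SDM process. That no described instrument is tied to the knowledge/attitude outcome is a separate labelling matter.

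**Conclusion.** The point holds in a limited form. The plan fixes a selection rule under which the single taped consultation per GP may not represent usual practice. Because GPs are unblinded and only one arm is trained, selection may differ by arm, and a difference in tape scores could not then be separated from it.

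The document settles neither size nor direction. The range of 0 to about 1.0–1.3 within-GP SD per GP, and the 0.5 SD example between arms, rest wholly on the assumed pool size and correlations. It would go too far to say that a bias has been shown, or that no part of a difference could be due to training.

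The point concerns a supplementary process measure. The primary outcome, the sample size and the clinical secondary outcomes are unaffected. The change is worth making because it is cheap and protects the only SDM evidence that is not self-reported.

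**What to change.** In Measurements, data collection, replace the sentence that lets GPs choose with a rule that the research centre names the visit in advance, in the same way in both arms. One workable form is the yearly visit of one patient drawn at random per GP within a fixed window, moving to the next patient on the drawn list if taping is refused. Refusals should be recorded by arm.

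Mask the observers to arm as far as the content of the recording allows. Removing labels will not mask fully, because the paper decision tool is used during intervention consultations and may be seen or heard on the tape.

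The cost is a changed instruction to GPs, a random draw at the centre, and some refusals and rescheduling; with only about 6 eligible patients per practice, the replacement list will be short if it is confined to study patients. No extra tapes or staff are needed. If tapes have already been made under the present rule, report them as GP-selected consultations and do not interpret them as usual practice.
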